### Reference standard of heart failure

Presence or absence of HF will be determined by an outcome panel consisting of two cardiologists and one GP. In analogy with earlier studies, the panel will use all available information from the diagnostic work-up, including echocardiography, but except the NT-proBNP results (to prevent incorporation bias pertaining to this particular test). Consensus diagnosis by an outcome panel is an established method in case an irreproachable reference standard is lacking, as is the case for HF [8,9]. Outcome panels have been successfully applied in earlier studies of HF by our group and the reproducibility of this method is high [13]. In case of no consensus the majority decision will be used. Patients classified as HF by the panel will be further classified as systolic or 'isolated' diastolic heart failure or 'isolated' right sided heart failure. For systolic heart failure, patients have to have an echocardiographic left ventricular ejection fraction ≤ 45% in combination with presence of symptoms indicative of heart failure (that is, orthopnoea, paroxysmal nocturnal dyspnoea, fatigue, peripheral oedema, nocturia more than twice a night, or any combination of these symptoms). For isolated diastolic ventricular dysfunction, patients have to have echocardiographic diastolic dysfunction and a left ventricular ejection fraction > 45%. For isolated diastolic heart failure patients have to have echocardiographic diastolic abnormalities in combination with indicative symptoms and signs (that is, peripheral or pulmonary fluid retention or raised jugular venous pressure) of heart failure [24] or indicative symptoms and echocardiographic left ventricular hypertrophy, atrial fibrillation, or anginal complaints [25].

### Assessment of diabetes

All patients registrated in the diabetic service of SHL have been diagnosed with diabetes according to the Diabetes Guidelines. The diagnosis diabetes was established if on two different days the fasting glucose level was above cut-off levels (6.0 mmol/l in capillary blood or 6.9 mmol/l in venous plasma or non-fasting glucose level > 11.0 mmol/l) or one glucose level > 11.0 mmol/l in combination with symptoms of hyperglycaemia, such as itching, thirst etc.

### Health status measurement

To assess the impact of (detecting and treating previously unknown) heart failure on the health status the participants will receive a questionnaire (including questions on health status) to be completed during their visit to the diagnostic centre at baseline. The group known with a cardiologist-confirmed diagnosis of heart failure will be visited at home. After 3 months and after 12 months from baseline measurement the participants will receive the same questionnaires, including an additional questionnaire with questions about possible change in medication.

In order to calculate quality-adjusted life years (QALYs) preference-based utilities will be measured with the EuroQol-5D instrument [26]. Generic health status will be assessed with the Short Form 36 (SF36) [27-29]. For disease specific health status the diabetes health profile (DHP) will be used [30]. These questionnaires are all widely tested and used.

### Cost-effectiveness analysis

A cost-effectiveness analysis of different strategies to detect unrecognized HF in patients with type 2 diabetes will be performed based on a social perspective according to international and national guidelines [31]. As a result of the primary data-analysis, various diagnostic strategies will be identified which differ in terms of the tests that are performed, the order of the tests, and the cut-off points used. Each strategy and each cut-off-point leads to different numbers of patients who are diagnosed as true positive (TP), false positive (FP), true negative (TN) and false negative (FN). To estimate the costs associated with these categories (FP, TP, FN, TN) a previously used and validated Markov model will be applied. The various strategies will be ranked by increasing cost-effectiveness ratios; the most optimal strategy in terms of cost effectiveness will be defined. It is important to note that there may be discrepancies in the most effective diagnostic strategy and the most cost-effective diagnostic strategy. The incremental cost-effectiveness of those tests that add to the best available diagnostic strategy, compared to the sub-optimal diagnostic strategy is of importance, in other words the additional value of the more expensive and most discriminating tests. For measuring direct costs, resource quantities are collected from the case record forms, and prices will be based on market prices or tariffs for the investigations performed in the study. Only relevant indirect medical costs are taken into consideration such as patient time and travel costs. When comparing diagnostic strategies, however, indirect costs are less relevant because all investigations can be performed in a single setting at the outpatient department, irrespective of the number of investigations. Both absolute costs and incremental costs of different diagnostic strategies will be taken in consideration.

A sensitivity-analysis will be performed in order to estimate the susceptibility of cost-effectiveness ratio's to variation in prior assumptions and choices, including a 'worst case - best case' comparison.

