## Abstract

**Background:**

We hypothesize that the prevalence of unknown heart failure in diabetic patients aged 60 years and over is relatively high (15% or more) and that a cost-effective strategy can be developed to detect heart failure in these patients. The strategy is expected to include some signs and symptoms (such as dyspnoea, orthopnoea, pulmonary crepitations and laterally displaced apical beat), natriuretic peptide measurements (Amino-terminal B-type natriuretic peptide) and possibly electrocardiography. In a subset of patients straightforward echocardiography may show to be cost-effective. With information from our study the detection of previously unknown heart failure in diabetic patients could be improved and enable the physician to initiate beneficial morbidity and mortality reducing heart failure treatment more timely.

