### Primary objectives

- To assess the prevalence of (previously unrecognised) HF in primary care patients with diabetes type 2 (DM 2).

- To establish the most cost-effective diagnostic strategy to detect unrecognised HF in these patients.

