### Statistical analysis

Prevalence of (previously unrecognised) heart failure (systolic and 'isolated' diastolic) will be calculated with exact 95% confidence intervals. The crude association of each diagnostic test (including the 'clinical score') with the presence or absence of HF will first be quantified by calculating predictive values, sensitivity, specificity and likelihood ratios by using univariate logistic regression analysis. Those with a p-value < 0.15 in the univariate analysis will subsequently be included in a multivariate logistic regression analyses to determine their independent contribution to the diagnosis of HF. In the analyses the chronology in which investigations are performed in practice will be followed. First of all, the diagnostic value of the signs and symptoms score will be assessed. Then NT-proBNP and ECG will be added, first separately and then in different combinations, to quantify their added diagnostic value, using the likelihood ratio test at a p-value of < 0.10 [32]. Areas under the ROC curve will be calculated for different combinations of the parameters to further quantify the diagnostic accuracy. Echocardiographic variables will not be evaluated separately on their diagnostic value because they would likely receive an overriding weight in the consensus judgement (i.e. diagnostic outcome assessment) [33]. In the cost-effective analysis, however, a separate diagnostic strategy to detect previously unrecognised HF by means of echocardiography only, will be evaluated, based on the echocardiographic findings. To assess the impact of heart failure, and diagnosis and treatment of heart failure in diabetes type 2 patients on health status, the scores on the Health status questionnaires of the three groups (no heart failure, known heart failure and previously unknown heart failure) will be compared at baseline (t0) and on 3 months and 12 months. Also the difference between 0-3 months, 3-12 months and 0-12 months within patients, will be compared between the groups (T-test and ANOVA).

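### As stated, the cost-effectiveness analysis can rank active testing strategies, but cannot show that active detection is cost-effective against current practice

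*Protocol article*

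**What the plan says.** All places are in the Protocol article.

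- **Strategies compared** (Cost-effectiveness analysis): "various diagnostic strategies will be identified which differ in terms of the tests that are performed, the order of the tests, and the cut-off points". The Statistical analysis section adds one more: "a separate diagnostic strategy to detect previously unrecognised HF by means of echocardiography only, will be evaluated". Every strategy named involves active testing.
- **Increments** (Cost-effectiveness analysis): "The incremental cost-effectiveness of those tests that add to the best available diagnostic strategy, compared to the sub-optimal diagnostic strategy is of importance".
- **Decision rule** (same section): "The various strategies will be ranked by increasing cost-effectiveness ratios; the most optimal strategy in terms of cost effectiveness will be defined". No reference for the ratio and no threshold is given.
- **Indirect costs** (same section): patient time and travel count as relevant in principle. They are then called less relevant when strategies are compared, because all tests can be done at one outpatient attendance however many there are.
- **Model** (same section): a Markov model supplies costs for true and false positives and negatives. A sensitivity analysis with worst and best cases is planned.
- **Aims**: the objective is "To establish the most cost-effective diagnostic strategy to detect unrecognised HF in these patients" (Primary objectives). The abstract's Background hypothesises "that a cost-effective strategy can be developed to detect heart failure in these patients".
- **Current care** (Study population): the diabetes service's standard care is described as glucose, HbA1c and other laboratory monitoring plus fundoscopy. It does not reappear in the economic analysis.

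**The concern.** Two questions are in play. The first is which testing strategy gives best value, given that some testing will be done. The second is whether looking actively for heart failure is worth its cost compared with what general practice does now. The objective asks the first; the abstract's hypothesis asks the second. The stated comparison is built for the first only.

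Ranking always produces a first place, whether or not any strategy is worth adopting. An add-on test can also look good value simply because the strategy it is added to is poor value. A reader of the final report is likely to take a named winner as grounds for introducing case-finding, and the analysis as described would not have tested that.

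**Working it through.** **The plan's own figures.** The only calculation in the document is the sample size: 9 × 10 = 90 cases; 90 / 0.15 = 600 participants; 600 / 0.50 = 1200 invitations. It reproduces and is not affected by this point. There are no economic figures to reproduce.

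**Is a usual-care reference stated?** The abstract, objectives, Health status measurement, Cost-effectiveness analysis and Statistical analysis sections contain no usual-care, no-testing or no-case-finding arm. The indirect-cost reasoning points the same way. Let *t* be patient time and travel for the visit, and C the other costs.

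- Between active strategies A and B: (C_B + t) − (C_A + t) = C_B − C_A, so *t* cancels.
- Against usual care without the visit: (C_B + t) − C_usual, so *t* stays.

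The visit lasts 1.5 hours and patients may live up to 60 km away, so *t* need not be small on the social perspective that the plan adopts. The argument for giving it less weight is valid only when every option includes the visit.

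**What the missing row looks like.** Taking the plan's 600 participants and 15% at face value: TP = 0, FP = 0, FN = 0.15 × 600 = 90, TN = 600 − 90 = 510. These are categories that the model already costs.

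**Illustration 1: the increment (all inputs assumed).** Per patient, relative to usual care, A costs EUR 100 and gains 0.0010 QALY; B costs EUR 150 and gains 0.0020 QALY.

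- A against usual care: 100 / 0.0010 = 100,000 per QALY
- B against usual care: 150 / 0.0020 = 75,000 per QALY
- B against A: (150 − 100) / (0.0020 − 0.0010) = 50,000 per QALY

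At an assumed threshold of 60,000, B passes against A, yet neither passes against usual care. With usual care in the comparison, A would be removed by extended dominance and B reported at 75,000.

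**Illustration 2: the ranking (all inputs assumed except the 15%).** Downstream cost is 2000 per TP and 250 per FP; q is the QALY gain per TP. Per patient:

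- TP = sensitivity × 0.15; FP = (1 − specificity) × 0.85
- cost = test cost + 2000 × TP + 250 × FP
- ratio against no case-finding = cost / (TP × q)

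For clinical score + NT-proBNP: TP = 0.80 × 0.15 = 0.12; FP = 0.20 × 0.85 = 0.17; cost = 80 + 240 + 42.5 = 362.5; at q = 0.05 the ratio is 362.5 / 0.006 = 60,417.

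| Strategy | Sens. / spec. | Test cost | Total cost | q = 0.20 | q = 0.05 | q = 0.01 |
|---|---|---|---|---|---|---|
| Clinical score | 0.70 / 0.70 | 50 | 323.8 | 15,417 | 61,667 | 308,333 |
| + NT-proBNP | 0.80 / 0.80 | 80 | 362.5 | 15,104 | 60,417 | 302,083 |
| + NT-proBNP + ECG | 0.85 / 0.80 | 110 | 407.5 | 15,980 | 63,922 | 319,608 |
| Echocardiography only | 0.95 / 0.95 | 250 | 545.6 | 19,145 | 76,579 | 382,895 |

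The order is the same in all three columns because q divides every ratio alike. The 20-fold spread in level simply reflects the 20-fold range assumed for q. The order alone therefore carries no information on whether the first-placed strategy is worth adopting; only the level against usual care does.

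**The case against.** The strongest reply is that this is a condensed article. Strategies are to be identified from the data, guidelines are cited, and the Markov model is an existing one; a reference arm may sit in the full protocol or the model documentation. The text calls the increment against a sub-optimal strategy important without saying that it is the only comparison. It does not say what the ranking ratio is taken against. If that were no testing, B in Illustration 1 would appear at 75,000 and the problem would be visible. This much stands: usual care is unstated, not ruled out. The reply does not remove the point, because the one comparator that is stated is another testing strategy and the indirect-cost reasoning presupposes active options throughout.

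Three stronger readings are tempting and not supported.

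- *That the primary economic objective fails.* It asks for the most cost-effective diagnostic strategy, and a ranking of strategies can largely answer that. The hypothesis that a cost-effective strategy can be developed stands only in the abstract; the hypothesis in the main Background concerns prevalence.
- *That usual care detects no heart failure.* The Study population section describes the diabetes service, not all general practice care, and the Background cites half of heart failure in primary care as undetected, so part is found.
- *That case-finding is poor value, or that the plan would accept B.* All costs, gains and thresholds above are assumed, and the plan has no acceptance rule.

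**Conclusion.** The point holds in limited form. The analysis as described can name the best of the testing strategies compared. It cannot show that active detection is cost-effective against current practice, as the abstract's hypothesis implies. This rests on the stated strategy set, the stated incremental comparator and the indirect-cost argument, all in the article; a reference arm in an unseen document would reduce the point to a wording matter.

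The size cannot be computed from the documents. The illustrations establish only that rank order and increments between testing strategies do not determine value against usual care. Sample size, data collection and the prevalence objective are unaffected. It is worth settling before the economic analysis is run, because it changes what that analysis may conclude.

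**What to change.** 1. Add usual care without active heart failure case-finding as the reference strategy in the existing model. It has no study-driven positives; panel-confirmed heart failure enters as undetected, with a rate of later routine detection.
2. Vary that rate over a stated range in the sensitivity analysis already planned.
3. Compute the first incremental ratio against this reference and later ones along the ordered strategies. State what the ranking ratio is taken against.
4. Include patient time and travel for the visit in every active strategy for the comparison with usual care.
5. If the reference is not added, limit the conclusion to the most cost-effective among the strategies compared, and do not claim that detection is cost-effective.

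The cost is one more row in the model, with no extra patients, tests or sample size. The downsides are one external assumption that the study does not supply, the routine detection rate, and a possibly less favourable headline.

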## Background

Cardiovascular diseases account for up to 80% of the excess mortality in patients with diabetes type 2 (DM2) [1]. Processes underlying this excess cardiovascular risk include coronary atherosclerosis, microvascular disease and autonomic neuropathy [1]. Importantly, morphological myocardial abnormalities and eventually diabetic cardiomyopathy and heart failure (HF), i.e. left ventricular dysfunction with symptoms of heart failure play a role [2,3]. Notwithstanding the high rate of cardiovascular diseases and the availability of morbidity and mortality reducing treatment for heart failure, [4] up to now, only a few studies assessed the prevalence of HF in diabetic patients. These studies showed a prevalence of HF of 12-22% in the subgroup of diabetic patients who had been admitted to the hospital [5,6]. In another study, the incidence rate of HF in DM2 patients was about 2.5 times higher than in non-diabetic control subjects [7]. Importantly, the diagnosis of HF in the aforementioned studies was based on hospital discharge diagnoses. To our knowledge, there are no studies that assessed HF using a diagnostic strategy including echocardiography in a representative sample of patients with diabetes in primary care (not selectively in those admitted to a hospital) [8,9]. Hence, valid prevalence estimates of HF in patients with diabetes type 2 are lacking. Such studies are needed because the majority of patients with diabetes is managed in primary care [10]. The diagnosis of HF however is notoriously difficult in the early phases of the syndrome and in the presence of co morbidities, such as chronic obstructive pulmonary disease (COPD) and obesity [11]. Moreover, echocardiography, the cornerstone investigation to diagnose HF, [4] is usually not ready at hand for primary care patients. Studies indicate that 50% of all patients (thus not only those with DM2) with HF in primary care remain undetected [10]. Recently, our group showed that unrecognised HF was common (prevalence 20.5%) among primary care patients with COPD aged ≥ 65 years [12]. High prevalence of unrecognised HF can therefore also be expected in patients with diabetes in primary care.

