### Diagnostic assessment

All participants will be investigated at the cardiology out-patient department of the regional hospital (Oosterschelde Hospital in Goes, the Netherlands) during a single 1.5 hour standardised diagnostic assessment. The diagnostic measurements include: history taking (e.g. orthopnoea), physical examination (e.g. pulmonary crepitations, laterally displaced apical beat), electrocardiography, and echocardiography. Plasma B-type natriuretic peptide measurements, glucose levels, creatinin levels, and HbA1C will be measured a few days later at a local 'medical checkpoint' in the neighbourhood of the participant, during their regular blood sample taking for the diabetes service. Signs and symptoms will be assessed by a trained physician in a standardised manner. The clinical findings will be combined in a 'clinical score' [13]. Present medication use is asked for and will be checked, patients will be asked to take their medication to the outpatient department. Medical history and time since diagnosis of diabetes with all diabetes related and not-related (e.g. NSAIDs) medication will be checked in the electronic medical files of the general practitioners (GPs). Blood samples (20 ml) will be taken and after centrifugation specimens of plasma and cells will be stored at -70 degrees Celsius. B-type natriuretic peptides (BNP and NTproBNP) are released predominantly from the ventricular myocardium in response to myocardial stretch, such as in heart failure [14]. The plasma level of both BNP and the release split product amino-terminal proBNP (NT-proBNP) are closely related to left ventricular function [15]. We will measure NT-proBNP levels from plasma using a non-competitive immunoradiometric assay (Roche Inc., Germany).

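### The cost-effectiveness analysis treats patient time and travel as nearly equal across strategies by assuming one outpatient session, which describes the research visit rather than the strategies compared

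*Protocol article*

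**What the plan says.** The relevant statements in the protocol article are these.

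- *Cost-effectiveness analysis, perspective:* the analysis "will be performed based on a social perspective according to international and national guidelines".
- *Same section, what is compared:* "various diagnostic strategies will be identified which differ in terms of the tests that are performed, the order of the tests, and the cut-off points".
- *Same section, time and travel:* "Only relevant indirect medical costs are taken into consideration such as patient time and travel costs". The next sentence reduces their weight when strategies are compared: "indirect costs are less relevant because all investigations can be performed in a single setting at the outpatient department", however many tests are done.
- *Same section, selection:* "The various strategies will be ranked by increasing cost-effectiveness ratios; the most optimal strategy in terms of cost effectiveness will be defined". Later sentences call the incremental cost-effectiveness of added tests important and say that both absolute and incremental costs will be considered. A sensitivity analysis with worst and best cases is planned.
- *Diagnostic assessment:* NT-proBNP and other blood values "will be measured a few days later at a local 'medical checkpoint' in the neighbourhood of the participant". The article adds that the sample is obtained "during their regular blood sample taking for the diabetes service".
- *Background:* echocardiography "is usually not ready at hand for primary care patients". The hypothesis paragraph expects direct echocardiography to pay off in only a subset of patients.
- *Study population:* invitees live within 60 km of the hospital.
- *Statistical analysis:* tests are evaluated in the order used in practice, and echocardiography alone is costed as a separate strategy.

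**The concern.** Time and travel can be played down between strategies only if every strategy needs about the same visits. The single-session argument supplies that premise, but it holds only for the research assessment, in which every participant goes to the hospital by design. A strategy that starts with a clinical score and a local blood sample, and refers only positives for echocardiography, needs a hospital trip for some patients. Echo-for-all needs one for every patient. From a social perspective, this is the comparison in which time and travel differ most.

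The direction of the error is predictable: the cost of echo-for-all is understated relative to local triage. Finding the most cost-effective strategy is one of the two primary objectives, so the costing rule bears directly on a headline result. In addition, the ranking sentence does not say which ratio decides.

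**Working it through.** **The plan's own figures.** The cost-effectiveness section contains no numbers. The base used here comes from the Power calculation section: 9 determinants × 10 events = 90 cases; 90 / 0.15 = 600 participants; 600 / 0.50 = 1200 invited. All three reproduce.

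**Step 1: hospital visits per strategy.** Prevalence is 15% (plan). Sensitivity (se) and specificity (sp) of local triage are assumed, because the article gives none. I also assume that the score and blood sample are obtained locally in practice.

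Share sent to hospital = 0.15 × se + 0.85 × (1 − sp)

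- Low end (0.80 / 0.80): 0.12 + 0.17 = 0.29, or 174 of 600.
- Central (0.90 / 0.60): 0.135 + 0.34 = 0.475, or 285 of 600.
- High end (0.95 / 0.40): 0.1425 + 0.51 = 0.6525, or about 392 of 600.

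Echo-for-all sends 600. Triage therefore spares about 208 to 426 trips, and 315 in the central case.

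**Step 2: effect on costs.** Assumed in addition: echocardiography EUR 100; sensitivity of echocardiography 0.98; local work-up L of EUR 30, 50 or 60; patient time and travel of T per hospital visit.

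- Triage cost = 600 × [L + 0.475 × (100 + T)]; cases found = 90 × 0.90 × 0.98 = 79.38.
- Echo-for-all cost = 600 × (100 + T); cases found = 90 × 0.98 = 88.20.
- Extra cases with echo-for-all = 8.82.
- The cost gap widens by 600 × 0.525 × T = 315 × T.

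| L | T | Triage cost | Echo-for-all cost | Difference | Per extra case |
|---|---|---|---|---|---|
| 30 | 0 | 46,500 | 60,000 | 13,500 | 1,531 |
| 30 | 20 | 52,200 | 72,000 | 19,800 | 2,245 |
| 30 | 40 | 57,900 | 84,000 | 26,100 | 2,959 |
| 50 | 0 | 58,500 | 60,000 | 1,500 | 170 |
| 50 | 20 | 64,200 | 72,000 | 7,800 | 884 |
| 50 | 40 | 69,900 | 84,000 | 14,100 | 1,599 |
| 60 | 0 | 64,500 | 60,000 | −4,500 | triage dominated |
| 60 | 20 | 70,200 | 72,000 | 1,800 | 204 |
| 60 | 40 | 75,900 | 84,000 | 8,100 | 918 |

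Each EUR 20 of time and travel adds 315 × 20 / 8.82 = EUR 714 per extra case, whatever L is. With L = 60 and no travel cost, triage costs more and finds fewer cases, so it would be discarded. It re-enters once T exceeds 60 / 0.525 − 100 = EUR 14.3. With L = 30, triage is the cheaper strategy at every T; only the price of the extra cases changes.

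**Step 3: why the deciding ratio must be named.** Take L = 50. Total cost per case found is 58,500 / 79.38 = 737 for triage and 60,000 / 88.20 = 680 for echo-for-all at T = 0, so echo-for-all ranks first. At T = 20 it is 809 against 816, so triage ranks first; the crossover is 50 / (0.90 − 0.475) − 100 = EUR 17.6. The incremental reading at T = 20 says instead that each extra case costs EUR 884 and leaves open whether that is worth paying. The two readings can select different strategies.

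**The case against.** **Time and travel are not excluded.** This is correct. A reader might infer that the plan sets them aside, but it counts them and only calls them less relevant between strategies. The planned sensitivity analysis could also vary them. However, it is described in general terms, does not name travel, and would not correct a base case built on the wrong visit pattern.

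**The evidence on blood sampling is mixed.** The abstract places blood tests within the single hospital assessment, and Table 1 lists NT-proBNP at baseline. But the Diagnostic assessment section, which is the detailed description, puts the sample at a later local draw. The point also does not depend on this alone: echo availability, the 60 km radius and the echo-only strategy remain.

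**The illustration is not the planned analysis.** The plan attaches costs to true and false positives and negatives with a Markov model and collects utilities for QALYs; cost per case found leaves that out. This stands as a limit on size. Downstream costs may dwarf the visit costs. They do not remove the gap of 315 × T, which adds to the cost difference whatever follows.

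**The plan does not say it ranks on average ratios.** A reader might infer this from the ranking sentence and conclude that the cheapest, least sensitive strategy must always win. Neither inference is supported. The article never specifies an average ratio, and it gives incremental cost-effectiveness a role. Even under average ratios, 'always' is false: at L = 50 and T = 0, echo-for-all costs more in total and still has the lower ratio. What remains is that the sentence does not say which ratio decides.

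**Threshold and comparator.** A willingness-to-pay value and a current-care comparator may stand in the full protocol or analysis plan. Their absence from an article is not a fault.

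**Conclusion.** The single-session reason conflicts with the article's own account of where tests are done and what is being compared. Under the assumed accuracy range, local triage needs 29% to 65% of the hospital visits of echo-for-all, so time and travel do not cancel. Treating them as nearly equal biases the comparison in favour of echo-for-all.

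It would go too far to say that the plan will name the wrong strategy. In the assumed settings, triage moves from dominated to admissible at about EUR 14 per visit when the local work-up costs EUR 60, while at EUR 30 it is the cheaper strategy throughout. All prices and accuracies are assumptions; only the 15% prevalence and the 600 participants come from the plan. The ranking sentence is ambiguous rather than wrong. Sample size, data collection and conduct are unaffected. This is a correction to make before the cost-effectiveness analysis is run, of moderate rather than critical weight.

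**What to change.** 1. Replace the single-session sentence with a costing rule. In the base case, each strategy is charged patient time and travel for the visits and settings it would need in practice. A hospital visit is charged only to patients whom that strategy sends to hospital, and a blood sample taken at a routine diabetes draw carries only its additional time and travel, if any.
2. Name time and travel per visit among the quantities varied in the planned sensitivity analysis.
3. In the ranking sentence, state that dominated strategies are removed first and that selection then rests on the incremental ratios that the section already calls important.

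The cost is a little more costing work: a visit pattern for each strategy and a unit price for time and travel. Invitees are selected on distance from the hospital, so their location should be known to the diabetes service. No extra patients, tests or visits are needed.
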